#### **9.1.1.2. Assessment of Severity**

The investigator will make an assessment of severity for each AE and SAE reported during the study. Severity refers to the grading of adverse events to assess the severity of symptoms as evaluated by the investigator or as experienced by the subject. The severity grading is independent of seriousness; in other words, a severe event is not necessarily serious.

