#### *AEs Occurring During the Infusion and up to 60 minutes from the End of Infusion*

The severity of AEs that occur during or less than 60 min after an infusion will be graded according to the criteria in Table 4.

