| SYSTEMIC                                                                                                                                                   |                                                        |                                                                                                              |                                                                                                                                               |
| Fever °F
(°C)                                                                                                                                                  | 99 to 101.2
(37.7 to 38.4)                          | 101.3 to 104
(38.5 to 40.0)                                                                               | >104
(40)                                                                                                                                  |
| Chills                                                                                                                                                            | Feels cold, slight shivering                           | Intermittent shaking                                                                                         | Continuous shaking, cold
and clammy skin                                                                                                   |
| Headache                                                                                                                                                          | Discomfort, but does not
require medication         | Responds to non-narcotic
analgesia                                                                        | Requires narcotic analgesia
or persistently recurrent
despite treatment                                                                 |
| Other pain                                                                                                                                                        | Discomfort, but does not
require medication         | Pain requiring non-
prescription medication.                                                              | Pain requiring prescription
and/or narcotic medication                                                                                     |

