| Nausea                                                                                                                                                            | Discomfort, but does not
require medication         | Can take fluids without
antiemetic medication                                                             | Little or no oral intake
and/or requires antiemetic
medication                                                                          |
| Vomiting                                                                                                                                                          | 1 episode                                              | 2 to 3 episodes                                                                                              | > 3 episodes                                                                                                                                  |

a This table applies to AEs associated with an infusion that occur during an infusion and/or up to 60 minutes after an infusion. The infusion rate at which the AE is observed will be recorded.

b If not accompanied by an increase in heart rate and subject is assessed as being comfortable or sleeping, blood pressure changes of this magnitude may be classified by the investigator as physiologic and not considered an AE.

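### Table 4 does not separate Mild from Moderate nausea, although Section 7.2.3 ties a mandatory infusion-rate reduction to Moderate (minor, wrong as written)

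*Protocol*

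**What the plan says.** Section 9.1.1.2 of the protocol states that severity is assessed "as evaluated by the investigator or as experienced by the subject". It directs that adverse events during an infusion, or less than 60 minutes after it, "will be graded according to the criteria in Table 4".

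The Nausea row of Table 4 has three cells:

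- **Mild** begins "Discomfort, but does not" and continues that medication is not required.
- **Moderate** begins "Can take fluids without" and ends with antiemetic medication.
- **Severe** is "Little or no oral intake" "and/or requires antiemetic" medication.

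Footnote a to Table 4 adds "The infusion rate at which the AE is observed will be recorded", but says nothing about an event that meets two cells.

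Section 7.2.3 (text below Table 3) uses the Table 4 grade as a trigger. For a Moderate or Severe event the rate is to be halved, or lowered to keep-open if necessary, until symptoms subside, and may then be resumed as tolerated. Nothing is prescribed for a Mild event, except that the rate must be advanced along Table 3 if it is tolerated. Section 9.1 names severity among the safety variables, and Section 10.4.1 lists it.

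**The concern.** A grading scale that triggers a mandatory action should give each event one grade. In the Nausea row the Mild cell is defined only by the absence of a need for medication. The Moderate cell is defined by being able to take fluids without an antiemetic. A subject who feels sick, is drinking and needs no antiemetic satisfies both.

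Two things are at stake. First, the severity recorded for such an event depends on which cell the grader reads first, and about 25 sites in three countries (Section 5.2) may settle it differently. Second, for an event during the infusion, one grade carries a compulsory rate reduction and the other does not. A statistical analysis plan cannot repair this later, because both the grade and the rate decision are made at the bedside under the protocol's wording.

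**Working it through.** **Logical check.** The Nausea row uses two attributes: oral intake (present, or little or none) and need for an antiemetic (no or yes). The four combinations, set against the cells and the rate rule in Section 7.2.3, are:

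| Oral intake | Antiemetic needed | Cells met | Rate action required |
|---|---|---|---|
| Present | No | Mild and Moderate | Halving (or keep-open) if graded Moderate; none if graded Mild |
| Present | Yes | Severe | Halving (or keep-open) |
| Little or none | No | Severe (the Mild wording is not excluded either, since it sets no intake condition) | Halving (or keep-open) |
| Little or none | Yes | Severe | Halving (or keep-open) |

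No combination is Moderate without also being Mild. An antiemetic need, which could have served as the dividing line, already makes the event Severe. The Mild cell sets no intake condition that could divide the two from below.

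**Comparison with a neighbouring row.** Other pain uses the same Mild wording, but its Moderate cell begins "Pain requiring non" and goes on to name non-prescription medication. There, a need for a drug divides Mild from Moderate. Vomiting is divided by number of episodes, and tachycardia, blood pressure and fever by numeric bands.

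**Illustration of the rate consequence.** The protocol states no figure for this, so there is none to reproduce. Inputs:

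- Dose per infusion: 1 g/kg (Section 7.2.1).
- Strength: 5 g per 100 mL (Section 3.1).
- Rates: 0.01, 0.02, 0.04 and 0.06 mL/kg/min for 15 minutes each, then 0.08 to the end (Table 3).
- Assumption, not in the protocol: the half rate is held for T = 15 to 60 minutes, and the infusion then returns to 0.08.

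Steps:

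1. Volume: 1 g/kg ÷ 0.05 g/mL = 20 mL/kg.
2. Given in the first 60 minutes: 15 × (0.01 + 0.02 + 0.04 + 0.06) = 1.95 mL/kg.
3. Remainder at top rate: (20 − 1.95) ÷ 0.08 = 18.05 ÷ 0.08 = 225.6 minutes.
4. Uninterrupted total: 60 + 225.6 = 285.6 minutes.
5. Halving 0.08 to 0.04 for T minutes leaves 0.04 × T mL/kg to make up, which takes 0.04T ÷ 0.08 = T/2 minutes.
6. T = 15: 7.5 minutes more, 7.5 ÷ 285.6 = 2.6%. T = 60: 30 minutes more, 30 ÷ 285.6 = 10.5%.

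The full 20 mL/kg is given in every case. The figures hold only for one event at 0.08 with a return to 0.08. They are not a bound for events at lower rates or for the keep-open option, because Section 7.2.3 leaves resumption to what the subject tolerates.

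**The case against.** The strongest reply is that Table 4 is an ordered scale and should be read across. The row then runs from discomfort alone, to nausea in which fluids are still possible, to failure of intake or need for an antiemetic. Severity is also expressly a matter of judgement by the investigator or experience of the subject, so graders are not testing each cell as a logical condition. This has force: the order does suggest that Moderate was meant as intake affected but fluids still possible, and clinical judgement would settle many cases. But neither cell says so, and judgement without a stated distinction is where sites can differ.

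A second reply is that the contrast with other rows is not perfectly clean. A headache that needed no drug but responded to a non-narcotic analgesic could also be argued either way. That is fair, and it is why the point is confined to the Nausea row, where the overlap covers every non-Severe event.

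Two stronger readings should be set aside:

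- A reader might infer that a Mild grade bars slowing the infusion. Section 7.2.3 does not say that. It makes advancement conditional on tolerance and is otherwise silent on Mild events, so an investigator may slow the infusion for either grade and the handling need not differ in practice.
- A reader might infer that safety conclusions or dosing are compromised. The documents do not support this. The summary counts in Section 10.4.1 do not depend on severity, and severity itself is only listed there. There is no concurrent arm between which grading could be biased, and a halving is cautious and reversible.

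**Conclusion.** The Nausea row is wrong as written, and the finding is minor. Nausea with oral intake present and no antiemetic need can validly be graded Mild or Moderate. During an infusion that difference decides whether a rate reduction is mandatory or left open. In the 60 minutes afterwards only the grade is affected.

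The consequence is limited to the severity listing and temporary rate handling. The primary and secondary efficacy results, the adverse event counts and the planned dose do not change. The added infusion time of 2.6% to 10.5% illustrates a single event under an assumed duration of halving and is not an estimate of effect on the trial. The protocol gives no nausea rate, so no number of affected events can be stated. The overlap itself rests on no assumption beyond reading the three cells as worded.

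**What to change.** Reword the Nausea row of Table 4 only:

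- **Mild:** discomfort, no medication needed, oral intake not reduced.
- **Moderate:** oral intake reduced but still able to take fluids, no antiemetic needed.
- **Severe:** little or no oral intake and/or antiemetic required.

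The matching case report form instruction should follow. Section 7.2.3 needs no change.

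A table-wide footnote that the highest applicable grade counts is not advised. On the present wording it would turn all non-Severe nausea into Moderate and leave Mild empty. With the row reworded it is unnecessary, and it would regrade other rows, such as the headache example above.

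The change needs no new data, visits or tests. Its costs are that nausea graded before the change may not be fully comparable with nausea graded after it, and that a few site queries may follow. Whether intake is reduced still calls for judgement during an infusion of just under five hours, but the cells would then state what is being judged.

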### 9.1.1.3. Assessment of Relationship

The investigator must provide his/her opinion of the relationship between GAMMAPLEX and the occurrence of each AE. The relationship of each AE will be categorized as follows:

- Not Related: Event for which sufficient evidence exists to conclude that the etiology is unrelated to the study product.
- Possibly Related: There is some temporal relationship between the event and the administration of the study product, and the event is unlikely to be explained by the subject's medical condition or other therapies.
- Probably Related: The temporal relationship between the event and administration of the study product is suggestive, and the event is less likely to be explained by the subject's medical condition or other therapies.
- Definitely Related: The event follows a reasonable temporal sequence from administration of the study product, follows a known or suspected response pattern to the product, is confirmed by improvement upon stopping the product (dechallenge) and reappears upon repeated exposure (rechallenge), if that occurs.

If an AE occurs that could equally be caused by GAMMAPLEX or other factors, the AE must be recorded as either Probably or Possibly related to GAMMAPLEX.

There may be situations when an SAE has occurred and the investigator has minimal information to include in the initial report. However, it is very important for the investigator to make an assessment of relationship for every event before transmission of the SAE form since it is used in determining expedited reporting requirements of the case to regulatory authorities. The investigator may change his/her opinion of causality as additional information becomes available and amend the SAE forms as necessary.

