#### *Suspected Unexpected Serious Adverse Events*

All AEs judged to be related to GAMMAPLEX that are both unexpected and serious (SUSARs) are subject to expedited reporting in the U.K. BPL will be responsible for reporting these to the concerned competent authorities.

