## **10.4. Safety Analyses**

### **10.4.1. Adverse Events**

The number of infusions in which an AE occurs during an infusion or within 72 hours after the infusion stops will be tabulated. A summary table including the following will be produced:

- number of subjects with AEs
- number of subjects with SAEs
- number of subjects who died
- number of subjects who withdrew because of AEs
- number of subjects with product-related AEs.

The nature, severity and frequency of all AEs will be listed.

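### In section 9.1.1.3, Possibly Related tests alternative causes at least as strictly as Probably Related, contradicts the equal-cause rule, and leaves some adverse events without a category

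*Protocol*

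**What the plan says.** Section 9.1.1.3 has four categories, and each definition makes its own demands.

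- To be marked *Not Related*, an event needs firm grounds against any product role. The wording is: "Event for which sufficient evidence exists to conclude that the etiology is unrelated to the study product".
- The lowest of the three related categories, *Possibly Related*, is satisfied by any link in time, however loose, but sets a demanding test for rival causes, namely that "the event is unlikely to be explained by the subject's medical condition or other therapies".
- One step up, *Probably Related* wants timing that points to the product. Its test for rival causes is worded differently: "the event is less likely to be explained by the subject's medical condition or other therapies".
- The top category, *Definitely Related*, adds a recognised response pattern, confirmation on stopping the product, and recurrence on re-exposure if that occurs.

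The section then adds a rule for events that GAMMAPLEX and other factors could equally have caused: "the AE must be recorded as either Probably or Possibly related to GAMMAPLEX".

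The classification is used in two places. Section 9.1.1.1, under suspected unexpected serious adverse events, states: "All AEs judged to be related to GAMMAPLEX that are both unexpected and serious (SUSARs) are subject to expedited reporting". Section 10.4.1 lists among its summary lines the "number of subjects with product-related AEs". Section 9.1.1.3 itself says that the relationship assessment feeds the decision on expedited reporting.

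**The concern.** A causality scale should demand more as it rises, and every event should fall into exactly one category. On alternative causes this scale does neither. The lower related category asks that other explanations be unlikely, while the higher one asks only that they be less likely. The space between *Not Related* and *Possibly Related* is left open.

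The trial is open-label and has no concurrent control arm, so investigator attribution carries much of the weight in separating product effects from background events. Competing explanations will be common: chronic ITP itself, and the stable corticosteroids, cyclophosphamide, azathioprine or attenuated androgens that section 6.1 permits. If sites settle the unclear cases differently, the product-related count in section 10.4.1 and the SUSAR status of unexpected serious events will depend partly on site habit.

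**Working it through.** No arithmetic applies to the definitions, so the check compares them clause by clause and then tries event types against them.

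**Step 1, temporal clause.** *Possibly* asks for some temporal relationship and *Probably* for a suggestive one. This rises in the expected order.

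**Step 2, alternative-cause clause.** *Possibly* asks that other explanations be unlikely; *Probably* that they be less likely. There are two readings of the second.

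- Less likely than the product as the cause. This is a weaker demand than unlikely, so the two categories are out of order.
- Less likely than under *Possibly*. The order is then kept, but the text states no such comparator, and *Possibly* still requires other causes to be unlikely.

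On either reading *Possibly* is too strict for the lowest related category.

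**Step 3, event types against the definitions.** All have some temporal link.

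| Event | Not Related | Possibly (definition) | Probably (definition) | Equal-cause rule |
|---|---|---|---|---|
| Other cause unlikely, timing not suggestive | no | yes | no | not needed |
| Product and other cause equally plausible | no | no: other cause is not unlikely | no: other cause is not less likely | sends it to Probably or Possibly |
| Other cause more likely, product not excluded | no: evidence not sufficient | no | no | not equal, so does not apply |

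*Definitely Related* does not take the third event either, because it needs a response pattern and confirmation on stopping the product.

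The second row is a contradiction: the rule assigns the event to categories whose definitions it fails. The third row is a gap: the event must be categorized, and no category or rule admits it.

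**Step 4, direction.** Marking the third event *Not Related* breaches that category's demand for sufficient evidence. Marking it *Possibly Related* breaches that category's demand that other causes be unlikely. Every choice breaks a definition, so the text does not decide which way investigators will go. Those who choose *Not Related* lower the product-related count and take an unexpected serious event out of the SUSAR definition; those who choose *Possibly Related* do not.

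**Step 5, weight of one subject.** Section 10.1 sets a minimum of 31 evaluable subjects. One subject reclassified moves the proportion with product-related events by 1/31 = 3.2 percentage points. The safety analysis also includes subjects excluded from efficacy (section 10.2), so with 31 evaluable subjects or more the shift per subject is at most this. It is a weight per subject, not an estimate of how many are affected.

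**The case against.** Three stronger readings are tempting, and the protocol does not support them.

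- *A reader might infer that the whole scale is inverted.* It is not. The temporal clauses rise correctly and *Definitely Related* adds further conditions. Only the alternative-cause clause is out of order, and the comparative reading of less likely would restore even that.
- *A reader might infer that plausible reactions in general have no category.* The equal-cause rule gives equally plausible events a related category. The gap is confined to events whose other cause is more likely but not established.
- *A reader might infer that product-related events will certainly be under-counted.* The bar for *Not Related* is high, and the equal-cause rule shows that the protocol leans towards relatedness. Under-counting is possible, not shown.

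The consequences are also limited by other provisions. Section 9.1.2 has all serious events from consent to 30 days after the last dose reported within 24 hours whatever their relationship, and section 9.1.3 has all of them passed to the sponsor and the FDA. The investigator may amend causality later, and section 9.1.1.4 lets the sponsor require further investigation of it. The count of infusions with an adverse event during or within 72 hours after infusion does not use causality. The product-related line is one of five descriptive lines in section 10.4.1, and no hypothesis test depends on it.

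These points limit the harm but leave the defect. Reporting all serious events captures them but does not settle SUSAR status, which turns on relatedness. The 72-hour measure does not cover later events, although section 9.1.1 collects adverse events to Day 90 or beyond. Nothing elsewhere in the protocol removes the contradiction or fills the gap.

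**Conclusion.** The point holds in three parts, all within section 9.1.1.3. The alternative-cause test for *Possibly Related* is at least as strict as that for *Probably Related*. The *Possibly* definition contradicts the equal-cause rule. Events with some temporal link, a more likely alternative cause and a product role not excluded fit no category.

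The result is inconsistent classification across about 25 sites, with possible under-counting of product-related adverse events and SUSARs. The size is unknown, because the protocol gives no basis for estimating how many events are affected. Primary and secondary efficacy are not touched. The conclusion rests on the ordinary meaning of unlikely and less likely; the comparative reading of the latter removes the ordering fault but neither the contradiction nor the gap. This should be corrected in the protocol, since investigators apply these definitions when they record each event.

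**What to change.** Reword section 9.1.1.3 so that the categories are ordered and exhaustive.

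- *Possibly Related*: some temporal relationship, a role of the product cannot be excluded, and the criteria for *Probably Related* are not met. This applies whether or not the subject's condition or another therapy could also account for the event.
- *Probably Related*: a suggestive temporal relationship, with other explanations unlikely.
- Equal-cause rule: such events are recorded as at least *Possibly Related*. This change is needed because the present rule allows *Probably* for an event whose alternative cause is as likely as the product, which would contradict the new *Probably* definition.

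*Not Related* can stay as it is. The new *Possibly* definition should not require that an alternative explanation exist; otherwise an event with only some temporal link and no alternative cause would lose the category it has now.

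The cost is two definitions, one rule and the matching CRF guidance. The downside is that slightly more events may be counted as product-related. The protocol refers to subjects enrolled before Version 7, so the change should also say whether causality already recorded is to be reviewed under the new wording.
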